## Abstract

**Background:**

Despite the efforts of the healthcare community to improve the quality of diabetes care, about 50% of people with type 2 diabetes do not reach their treatment targets, increasing the risk of future micro-and macro-vascular complications. Diabetes self-management education has been shown to contribute to better disease control. However, it is not known which strategies involving educational programs are cost-effective. Telehealth applications might support chronic disease management. Transferability of successful distant patient self-management support programs to the Belgian setting needs to be confirmed by studies of a high methodological quality. “The COACH Program” was developed in Australia as target driven educational telephone delivered intervention to support people with different chronic conditions. It proved to be effective in patients with coronary heart disease after hospitalization. Clinical and cost-effectiveness of The COACH Program in people with type 2 diabetes in Belgium needs to be assessed.

**Methods/Design:**

Randomized controlled trial in patients with type 2 diabetes. Patients were selected based on their medication consumption data and were recruited by their sickness fund. They were randomized to receive either usual care plus “The COACH Program” or usual care alone. The study will assess the difference in outcomes between groups. The primary outcome measure is the level of HbA1c. The secondary outcomes are: Total Cholesterol, LDL-Cholesterol, HDL-Cholesterol, Triglycerides, Blood Pressure, body mass index, smoking status; proportion of people at target for HbA1c, LDL-Cholesterol and Blood Pressure; self-perceived health status, diabetes-specific emotional distress and satisfaction with diabetes care. The follow-up period is 18 months. Within-trial and modeled cost-utility analyses, to project effects over life-time horizon beyond the trial duration, will be undertaken from the perspective of the health care system if the intervention is effective.

**Discussion:**

The study will enhance our understanding of the potential of telehealth in diabetes management in Belgium. Research on the clinical effectiveness and the cost-effectiveness is essential to support policy makers in future reimbursement and implementation decisions.

**Trial registration:**

Belgian number: B322201213625. ClinicalTrials.gov Identifier: NCT01612520

## Background

The increasing prevalence of type 2 diabetes poses a challenge to health care systems. Type 2 diabetes is a complex illness that requires continuing medical care and patient self-management education to reduce the risk of long-term complications [1]. Despite the efforts of the healthcare community to improve the quality of diabetes care, about 50% of the population with type 2 diabetes do not reach the guideline recommended treatment targets [1,2]. A recent comparative research of quality improvement strategies in diabetes care found that interventions targeting the system of chronic disease management along with the patient are likely to be more beneficial than those strategies targeting solely health-care professionals [3].

Patient education in disease self-management is commonly recognized as an essential part of diabetes treatment. It has been shown to improve glycaemic control, whereby the intensity of the educational program is believed to be an important predictor of the outcomes [4-6]. However in Belgium, the majority of people with type 2 diabetes are not offered coverage of educational programs. Current evidence of the cost-effectiveness (CE) of diabetes education is limited due to scarcity of publications in this area and the poor quality of the studies [7-9].

A variety of strategies and techniques can be used to provide adequate education in development of problem-solving skills in diabetes management. Offered in a group or individually [10,11]; face-to face or on distance [12-15]; led by people with or without special professional training [16,17]; and depending on the curriculum, - educational programs may demonstrate different results in terms of the clinical and cost-effectiveness. The complexity of these interventions make it difficult to detect the direct effect of specific features of patient education on the outcomes [18,19]. Since a commonly accepted reporting methodology for interventions in prevention and health promotion within clinical trials is lacking, patient education programs are frequently poorly described and difficult to reproduce in other settings.

“The COACH Program” is a well-established target-driven telephone intervention delivered by nurses or dieticians who undergo special additional training [20]. It showed to effectively reduce the disease related risk factors in patients with established coronary heart disease after hospitalization [21,22]. After a research phase, The COACH Program became operational in Australia and extended its curriculum to ten different chronic conditions including type 2 diabetes, in the past 15 years. The clinical and cost-effectiveness of The COACH Program has not yet been tested in Europe.

The specific aims of the study are: 1) to assess whether The COACH Program can be offered by a sickness fund and delivered in cooperation with caregivers in Belgium; 2) to investigate whether The COACH Program helps people with type 2 diabetes to achieve better glycemic control and improved modifiable diabetes risk factors and self-perceived health compared with usual care alone; 3) to analyze the cost-effectiveness of The COACH Program from the perspective of the health care system based on the trial results extrapolated to a life-long horizon.

## Methods/Design

### Study design

The study is a parallel-group RCT, in which patients with type 2 diabetes, affiliated to the Belgian sickness fund Partena, were selected based on their medication consumption data, recruited by their sickness fund, and randomized to receive usual care plus The COACH Program or the usual care alone. The study will assess the difference in outcomes between the two groups. The primary outcome measure is the level of glycohemoglobin HbA1c at 6 months after randomization. The secondary outcomes are: total cholesterol (TC), low-density lipoprotein (LDL), high-density lipoprotein (HDL), triglycerides (TG), blood pressure (BP), Body Mass Index (BMI), smoking status; proportion of people at target for HbA1c, LDL-Cholesterol and Blood Pressure; self-perceived health status, diabetes-specific emotional distress, and satisfaction with diabetes care. The follow-up period is 18 months. All outcome measurements will be collected 3 times: before randomization, upon the graduation from the program (6 months after the program start); and at the end of the follow-up period (18 months after randomization). The allocation ratio is 1:1. Within-trial and modeled cost-utility analyses, - to project effects over a longer time horizon beyond the trial duration, - will be undertaken from the perspective of the health care system if the intervention is effective.

### Study participants

Study participants are adults between 18 and 75 years old with a diagnosis of type 2 diabetes taking glycaemia lowering oral and/or injectable medications. Exclusion criteria are people on corticoid therapy and/or with a debilitating coexisting medical condition such as dialysis, mental illness, cancer; residents of long term care facilities; pregnant women; and people incapable of telephone communication in Dutch.

### Coaching intervention

The COACH Program consists of 5 monthly telephone sessions of 30 minutes on average delivered by certified diabetes nurse educators (further referred to as “coach”). Prior to the intervention, they undergo 5-days training in up-to date clinical guidelines on diabetes self-management and how to give patients the motivation and the skill to improve their risk factors. Coaches are also trained in the use of the COACH Program software for patient administration. Coaches use patient’s baseline data obtained during the first home visit, to assess the individual risk profile and to suggest targets for diabetes risk factors based on the Flemish and international guidelines for good practice in diabetes care [1,23-25]. The therapeutic goals are discussed with the GP by phone before the first coaching session.

Prior to the beginning of the coaching, patients of the intervention group receive a welcome package with information about the program, a book with advice on nutrition in diabetes and a waist circumference meter with a BMI calculator. Patients with HbA1c above 6% (42 mmol/mol) at baseline, who are not in possession of an insurance-covered meter for self-monitoring of blood glucose (SMBG), receive a SMBG set including lancets and strips.

All risk factors associated with diabetes are addressed by the coaches, - glycaemia, lipids, blood pressure, kidney, foot and eye checks, nutrition, physical activity, smoking and alcohol consumption. Patients are instructed on how to perform SMBG and interpret the results. A measurement frequency of one or two day profiles a week is advised. Depending on the type of the diabetes medication – causing hypoglycemia or not – a scheme of four or two times a day respectively is recommended. Considering special skills needed to assist people in smoking cessation, smokers of the intervention group are motivated to contact the tobaccological service of the Belgian Cancer Federation “Tabakstop” that offers tailor-made telephone sessions and is free for all patients.

The coach registers and monitors the biomedical risk factors, the lifestyle/behavioral parameters and the use of the recommended medications. The COACH Program software supports advice on individual treatment targets and the frequencies for the diabetes risk factors control. The software also helps to quickly generate a written coaching report with actual advice and comparison of the current status of the risk factors against the individual treatment targets. These reports are sent to the patients and copied to their GP’s by e-mail or post. The COACH Program software is built upon several databases, such as reimbursed medications and standard comments for each diabetes risk factor.

The COACH Program trains patients to ‘drive’ the process of achieving and maintaining the target levels for their risk factors while working in association with their GP. Coaching is focused on eliminating the knowledge and treatment gap and motivating the patient to apply the appropriate lifestyle and medical therapy. Each session is used as the foundation for the next contact. The coaching model is a continuous five-stage coaching cycle: stage 1 - finding out what the patient knows; stage 2 - telling the patient what he/she should know; stage 3 - assertiveness training; stage 4 - setting an action plan; stage 5 - reassessment at the next coaching session (monitoring). Patients are invited to contact their coach between coaching sessions for questions and further information if required.

### The control group

The control group receives usual care alone. In Belgium, patients on oral glycaemia lowering medications are predominantly treated by their GPs. When insulin therapy needs to be initiated patients become entitled to a “diabetes care trajectory” reimbursed by the national health insurance. The care trajectory is initiated by the GP and implies coordinated care, including diabetes education by a certified diabetes educator, and a yearly contact with an endocrinologist, in addition to the regular GP visits. Patients with advanced diabetes, in need of three or more insulin injections per day, are normally treated in a hospital setting by an endocrinologist, with support of a multidisciplinary team.

All study participants, including the control group, receive a DVD with educational material on type 2 diabetes, its complications and lifestyle recommendations. The laboratory results of the blood analysis are mailed to all study participants and their GPs after each assessment.

### Patient recruitment and randomization

Patients were selected from the administrative database of the sickness fund “Partena” which belongs to the Group of the Independent Sickness Funds, based on the reimbursement data of glycaemia lowering medications in the past 12 months. Prior to the start of patient recruitment, their GP’s were informed about the study by mail. Selected patients were sent a letter of invitation to participate in the study and invited to express their interest by returning an attached response card. Those candidates who expressed their interest, or have not reacted to the invitation within two weeks, were contacted by phone. A home visit for the baseline assessment was scheduled with those patients who confirmed their participation. The assessment visit was carried out by a nurse not involved in the intervention delivery.

Randomization was performed every 2 weeks on average. To achieve a comparable HbA1c distribution within both groups, patients were stratified based on the baseline level of HbA1c: with HbA1c < 7% (53 mmol/mol), or with HbA1c ≥ 7%. Patients from both strata’s were allocated to the intervention or the control group by a data analyst of the Independent Sickness Funds, further not involved into the study, by using a random number generator programmed in Excel.

### Data collection and analysis

During the assessment visits, the nurses register data as stated in Table 1. Weight is measured by electronic scale, patients wearing light indoor clothing, no shoes. Height is measured in the standing position using a portable anthropometer, feet, knees, buttocks and shoulder blades in contact with the vertical surface, no shoes. Waist circumference is measured with a measuring tape according to the guidelines of the Belgian Association for the Study of Obesity [26]. Blood pressure is taken in a sitting position by using a manual sphygmomanometer. Two measurements are taken, the lower systolic and diastolic measurements will be used in the analysis. The level of toxic carbon monoxide (CO) is measured in parts per million (ppm) by a CO meter in addition to self-reporting smoking status.

**Table 1 T1:** Patient data collection at three assessment moments during the trial

**Patient data**	**Method of collection**	**Baseline (T0)**	**T0 + 6 months**	**T0 + 18 months**
Gender	Sickness funds database	x		
Age	Sickness funds database	x		
Education	Self-reporting	x		
Occupation	Self-reporting	x		
Diabetes 2 since	Self-reporting	x		
Comorbidities:	Self-reporting	x		x
*Cardiovascular:* CHD; heart failure; atherosclerosis; past MI; stroke; TIA				
*Respiratory:* COPD; asthma				
*Other:* hypoglycemia; hypertension; dyslipidemia; Kidney disease; neuropathy; depression				
Family history of type 2 diabetes and cardiovascular disease	Self-reporting	x		
Blood pressure	Home visit test	x	x	x
Height	Home visit test	x		
Weight	Home visit test	x	x	x
BMI	Calculated	x	x	x
Waist circumference	Home visit test	x	x	x
Prescribed medications	Sickness funds database + self- reporting	x	x	x
Smoking	Self-reporting + CO test	x	x	x
Lifestyle: physical activity; alcohol consumption; healthy eating	Self-reporting	x	x	x
Diabetes risk factor knowledge test	Self-reporting	x	x	x
EQ-5D	Self-reporting	x	x	x
PAID	Self-reporting	x	x	x
DTSQ – status version	Self-reporting	x	x	x
HbA1c	Pathology lab	x	x	x
Lipid profile: TC; HDL; LDL; TG	Pathology lab	x	x	x
Satisfaction about the COACH program (Intervention group)	Self-reporting		x	
Costs	Sickness funds database; time& material sheets; contracts	x	x	x

*Abbreviations: **CHD* Coronary Heart disease, *MI* Myocardial Infarction, *TIA* Transient Ischemic Attack, *COPD* Chronic Obstructive Pulmonary Disease, *EQ-5D* EuroQol 5 dimension health status questionnaire, *PAID* Problem Areas in Diabetes Questionnaire, *DTSQ* Diabetes Treatment Satisfaction Questionnaire; *HbA1c* glycohemoglobin, *TC* total cholesterol, *HDL* high-density lipoprotein, *LDL* law-density lipoprotein, *TG* triglycerides.

The patients are asked to fill in the EQ-5D 3-L as a generic health status survey, the questionnaire Problem Areas in Diabetes (PAID) that measures the level of diabetes-specific emotional distress, and the Diabetes Treatment Satisfaction Questionnaire (DTSQ). All chosen instruments have a well-established cross-cultural validity. In addition, patients in the intervention group are asked to fill in a specific satisfaction questionnaire about The COACH Program. The blood samples are collected and delivered to the laboratory “Meidina Medische Analysen” contracted for the period of the trial. For the biomedical analyses the following methods are used: HbA1c – by ion exchange chromatography; TC and TG – by enzymatic colorimetric methods; HDL – through neutralization of LDL and VLDL. The LDL is calculated using the Friedewald equation. Table 1 summarizes the protocol of patient data collection during the trial.

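### The intervention-only COACH satisfaction form, listed among the data nurses register at the 6-month visit, probably reveals the arm to the assessor who reads blood pressure manually

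*Protocol article*

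**What the plan says.** All references are to the protocol article.

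- **Who records.** Data collection and analysis: "During the assessment visits, the nurses register data as stated in Table 1".
- **The arm-specific item.** Table 1 has a row "Satisfaction about the COACH program (Intervention group"), collected by self-report and marked only at T0 + 6 months. The text below the table says that "patients in the intervention group are asked to fill in a specific satisfaction questionnaire about The COACH Program", in addition to the EQ-5D, PAID and DTSQ that both arms complete.
- **Blood pressure.** "Blood pressure is taken in a sitting position by using a manual sphygmomanometer". Then: "Two measurements are taken, the lower systolic and diastolic measurements will be used in the analysis". Table 1 lists it as a home visit test at baseline, 6 and 18 months. Study design names blood pressure and the proportion at blood pressure target as secondary outcomes.
- **Assessor.** Patient recruitment and randomization: "The assessment visit was carried out by a nurse not involved in the intervention delivery". This sentence directly follows the one on scheduling the baseline home visit, which takes place before randomisation.
- **Primary outcome.** Study design: "The primary outcome measure is the level of glycohemoglobin HbA1c at 6 months after randomization". It is measured in a contracted laboratory.

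**The concern.** A manual blood pressure reading depends on the observer. If the nurse at the 6-month visit also handles a form that only intervention patients receive, then its presence or absence tells the nurse the arm. An expectation that coached patients have improved could then shift readings in one direction in one arm. Such a bias would pass into both mean blood pressure and the share of patients at target, at the same time point as the primary outcome.

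The independent nurse does not settle this. The sentence describes the baseline visit, where there is no allocation to know. Even if the arrangement continues at follow-up, a nurse who does not deliver the coaching is not the same as a nurse who does not know the arm. The article does not say that follow-up assessors are masked.

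**Working it through.** **1. Reading the passages together.** Nurses register the Table 1 data at the visits. One Table 1 row belongs to one arm only and is marked at 6 months only. Manual blood pressure is marked at the same assessment. No other route for the form (post, sealed envelope, other staff) is described. The direct inference is that the visit nurse meets the form in one arm and not in the other. The article does not state this outright.

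**2. Which outcomes are exposed.**

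| Outcome at 6 months | How obtained | Exposure through this form |
|---|---|---|
| HbA1c, lipids | Laboratory | Little |
| Blood pressure, share at target | Nurse, manual device | Yes |
| Waist circumference | Nurse, measuring tape | Some |
| EQ-5D, PAID, DTSQ | Patient, who knows the arm | Largely independent of the form |

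At 18 months the form is not used, so this mechanism does not apply there.

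**3. The plan's sample size, for the number per arm.** Inputs from Sample size: difference 0.3%, SD 1.05%, power 0.90, alpha 0.05 (two-sided, as the tests are two-tailed).

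n per arm = 2 × (1.960 + 1.282)² × 1.05² / 0.3² = 257.4, rounded up to 258, or 516 in total. The plan states 514, so its figure is reproduced closely. I use 514 / 2 = 257 per arm.

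**4. Illustration for systolic pressure.** The baseline SDs in Table 2 are 18 and 17 mmHg. I assume 17.5 mmHg at 6 months.

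SE of the difference = 17.5 × √(2/257) = 1.54 mmHg

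Difference that reaches two-sided p = 0.05: 1.96 × 1.54 = about 3.0 mmHg

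If there is no true effect but a constant observer shift d in one arm, the rejection rate is P(|Z + d/SE| > 1.96):

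| Assumed shift d | d/SE | False-positive rate |
|---|---|---|
| 0 mmHg | 0 | 5% |
| 1 mmHg | 0.65 | about 10% |
| 2 mmHg | 1.30 | about 25% |
| 3 mmHg | 1.94 | about 49% |

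The shifts are assumptions. The documents give no figure for observer bias, so the table shows how sensitive the test is to a shift and not how large a shift to expect.

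**The case against.** **Disclosure is inferred, not stated.** The reference to Table 1 cannot be literal for every row. The table also holds age and gender from the sickness fund database, laboratory results, and costs from contracts and time sheets. The satisfaction row says only that it is self-reported. The article does not say who hands the form out, who collects it, or whether the nurse sees it, and the full protocol may route it separately. This stands, and it is why the point says *probably*. A reader might infer that the nurse must know the arm, but the text does not go that far.

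**Nothing is contradicted.** The article does not claim masked assessment. This is true. The point concerns an avoidable weakness in a procedure and not an inconsistency.

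**The nurse may learn the arm anyway.** Visits take place in the home, where intervention patients may have the welcome package, the nutrition book, sometimes a glucose meter, and written coaching reports. Patients may also talk about their coach. This stands too: the added bias from the form alone is smaller than the total and cannot be estimated. It does not justify building in a cue for every intervention patient.

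**Three stronger readings lack support.**

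- A reader might infer that the form primes the answers on the EQ-5D, PAID and DTSQ. No order of completion is stated, and both the text and Table 1 list the form after those instruments.
- It follows that a bias carried by this form into the QALYs is not supported either. Those instruments are answered by patients who know they were coached, and moving one form would not change that.
- A reader might see in Table 2 that 56% of patients have diastolic pressure below 80 mmHg, fewer than a normal curve with the printed means and SD would give, and infer observer bias. Those readings precede randomisation and the share is the same in both arms. At most they suggest rounding that is unrelated to arm.

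**Conclusion.** The point holds as a specific, avoidable route by which the 6-month assessor probably learns the arm. It bears mainly on manually read blood pressure and the proportion at blood pressure target, with waist circumference a lesser case. The primary outcome and the lipids are little exposed, and the 18-month visit is untouched by this form.

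The size of any bias is unknown. The 25% false-positive rate at 2 mmHg rests on an assumed shift, an assumed 6-month SD of 17.5 mmHg, 257 completers per arm and an unadjusted comparison. The conclusion also assumes that the nurse handles or sees the form, as the plain reading suggests. If the full protocol routes it elsewhere, one sentence saying so removes this route. The change is worth making because it costs almost nothing, not because the trial's main result is in doubt.

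**What to change.** - Take the COACH satisfaction form out of the nurse visit: post it to intervention patients and have it returned to the programme office. If that is not practical, give it only after blood pressure, waist circumference and all common questionnaires have been recorded.
- Do not give visit nurses the allocation at 6 or 18 months, and state the assessors' masking status at both visits.
- Recruitment ran from April 2012 to June 2013, so 6-month visits would fall roughly between October 2012 and December 2013. For visits already done, report whether the assessors knew the arm and interpret the 6-month blood pressure results in that light.

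**Cost.** At most one mailing to the 287 intervention patients and a change to the visit worksheet. The return rate may be somewhat lower, on a questionnaire that is not compared between arms. A change during the trial would mix two modes of collection. Some patients will still reveal their arm, so the change reduces disclosure but does not guarantee masking.
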